## **2.6 Study outcomes**

The primary outcome for this study will be presentation at the GP practice. For each adult who is enrolled in the study and given information about the GPCC, we will determine whether they presented at one of the GP practices.

Secondary outcomes will include the following:

- HIV testing uptake: We will assess whether participants complete HIV testing at GP practices. This outcome will be defined for all adults who are enrolled in the study.
- HIV-positivity among participants who get tested for HIV.
- Linkage to care among newly diagnosed individuals. We will assess whether participants who tested HIV-positive initiate ART at the GP practices.

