### **1.5 Study objectives**

To determine whether HTS demand creation material that leverages behavioural science principles will increase the demand for HIV testing at GP practices.

The primary outcome will be presentation at the GP practice. Secondary outcomes will include HIV testing uptake, yield of new HIV-positive diagnoses, and yield of PLHIV who initiate ART.

This will be a randomized controlled trial to rapidly test two different low-cost demand creation

interventions among adults residing in the catchment areas of GPCC programme clinics. There will be three study groups:

1. For one group of participants, free HIV testing will be bundled with other health services that might be desired. Participants will receive a brochure that advertises the opportunity to receive free blood pressure testing and rapid glucose testing along with free HIV testing (Appendix 1). This approach seeks to address stigma associated with HIV testing while also offering other health services that people value.
2. For a second group of participants, the value of HIV testing will be emphasized using a 100 Rand voucher (US\$ 6.67) that can be redeemed for free services (Appendix 2). This approach highlights the monetary value of the free services and seeks to leverage an endowment effect and loss aversion.
3. A third group of participants will receive the standard of care promotion materials for HIV testing. The standard of care (SOC) community demand procedure includes distributing a Your Care Network (YCN) brochure that advertises free HTS and free ART services for those that test positive (Appendix 3), a website ([www.yourcarenetwork.co.za](http://www.yourcarenetwork.co.za)), a YCN Facebook page and standard signage and posters outside participating GP practices.

We will examine the effect of demand creation interventions on the likelihood that individuals will visit GP practices and utilize HIV services. We will also examine the effect of the interventions on identification of newly diagnosed PLHIV.

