## **2.7 Sample size**

We anticipate that about 5% of participants in the standard of care group will present at the GP. This is a conservative assumption based on the experiences of similar campaigns in which individuals are approached in the community. With 2,400 adults randomized to each of the three study arms (total sample size of 7,200 adults), we will have >80% power (alpha=0.05, 2-sided) to detect a difference of at least 2 percentage points in attendance at GP practices.

However, since there is a possibility that a larger proportion of participants in the standard of care group will present at the GP, we have selected a sample size of 4,000 adults per arm (12,000 total) as this will ensure there is 80% power to detect a difference of at least 2 percentage points.

A small difference in the primary outcome would be meaningful given the low cost of the demand creation interventions. With 5 field workers distributing materials over a period of 10

weeks, ), the target of 12,000 adults reached by the field workers can be achieved by enrolling 48 individuals per day (which is feasible given the small amount of time needed to enrol an individual). HTS services at the GP practice will also start at the same time as the field work but will run for a period of 12 weeks. Provision of services at the GP practices will continue for an extra 2 weeks following the end of field work in order to allow individuals with the marketing material to still access HTS.

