## **2.10 Data Analysis**

Primary analysis: We will compare the primary outcome between study arms. We hypothesize that presentation at GP practices will be higher in the two intervention arms than in the standard of care arm. We will test for significant differences in the primary outcome between each of the intervention groups and the standard of care group using logistic regression analyses.

Secondary analyses: We will also compare the secondary outcomes in each intervention group to the standard of care group using logistic regression analyses. Our hypothesis is that HIV testing uptake will be higher in the intervention groups than the standard of care group.

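### Two of the three secondary outcomes are compared between arms within groups formed after randomisation, so they do not measure the interventions' effect on case finding or ART starts

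*Protocol*

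**What the plan says.** The Summary and section 1.5 of the Protocol list the secondary outcomes in the same terms: "Secondary outcomes will include HIV testing uptake, yield of new HIV-positive diagnoses, and yield of PLHIV who initiate ART". Section 1.5 adds that the trial will examine how the interventions affect the finding of newly diagnosed people.

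Section 2.6 makes the three outcomes operational:

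- Testing uptake is defined for all enrolled adults.
- The second outcome is "HIV-positivity among participants who get tested for HIV".
- The third is "Linkage to care among newly diagnosed individuals", assessed as ART initiation among participants with a positive test.

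Section 2.10 treats all three alike: "We will also compare the secondary outcomes in each intervention group to the standard of care group using logistic regression analyses". Its only stated secondary hypothesis is that testing uptake will be higher in the intervention groups.

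**The concern.** Whether a person tests, and whether a person is diagnosed, is settled after the envelope is handed over. The materials are designed to influence both. Sections 1.4 and 1.5 say the bundled screen should lessen stigma and appeal to people who value other services, and that the voucher should make the value of the service salient. The people who test may therefore differ in HIV risk between arms. The tested and the diagnosed are then not randomised groups, and a logistic regression within them mixes the effect of the material with differences in who turned up.

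Section 2.6 also contains no outcome that counts diagnoses or ART starts per adult enrolled, so the case-finding aim in section 1.5 has no matching measure. An arm that finds more people with HIV could show the same or a lower positivity, and a reader of the secondary results could conclude that it did no better.

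**Working it through.** **The plan's own figure.** Section 2.7 assumes that "about 5% of participants in the standard of care group will present at the GP" and seeks "a difference of at least 2 percentage points in attendance at GP practices", with two-sided alpha 0.05. For two proportions with n per arm, difference d and mean proportion p̄, power = Φ{[d√n − 1.96√(2p̄(1−p̄))] / √(p₁(1−p₁)+p₂(1−p₂))}. With n = 2,400, 5% v 7% and p̄ = 6%: (0.9798 − 0.6583)/0.3356 = 0.958, so power is 83.1%. The stated figure of more than 80% reproduces and is not in dispute.

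**Inputs for the illustration**

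- From the Protocol: 4,000 per arm, and 5% v 7% presenting (section 2.7).
- Assumed: every presenter tests; the intervention adds testers without displacing those who would have come anyway; positivity under standard of care is 12%. Table 1 gives 12% as a provincial prevalence estimate. The Protocol gives no positivity among testers.
- Varied: positivity x among the extra testers.

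**Positivity.** Tested: 4,000 × 5% = 200 v 4,000 × 7% = 280, so 80 extra testers. Cases: 200 × 12% = 24 v 24 + 80x. The first odds ratio (OR) is among the tested, the second among all 4,000.

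| x | Cases | Positivity among tested | OR, tested | Cases per enrolled adult | OR, all enrolled |
|---|---|---|---|---|---|
| 0% | 24 v 24 | 12.0% v 8.6% | 0.69 | 0.60% v 0.60% | 1.00 |
| 3% | 24 v 26.4 | 12.0% v 9.4% | 0.76 | 0.60% v 0.66% | 1.10 |
| 5% | 24 v 28 | 12.0% v 10.0% | 0.81 | 0.60% v 0.70% | 1.17 |
| 6% | 24 v 28.8 | 12.0% v 10.3% | 0.84 | 0.60% v 0.72% | 1.20 |
| 12% | 24 v 33.6 | 12.0% v 12.0% | 1.00 | 0.60% v 0.84% | 1.40 |

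The 5% row in full: OR among the tested = (28/252)/(24/176) = 0.81; OR among all enrolled = (28/3,972)/(24/3,976) = 1.17.

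The last row needs no difference in risk. With equal positivity the conditional comparison shows nothing, although 33.6/24 = 1.40, that is, 40% more cases.

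**A lower base.** With 5% positivity under standard of care there are 10 cases. Extra testers at 3% give 10 v 12.4 cases, with ORs of 0.88 (tested) and 1.24 (all enrolled). At 5% they give 10 v 14 cases (1.00 and 1.40). At 6% they give 10 v 14.8 cases (1.06 and 1.48), so here the two measures agree in direction.

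**Linkage.** Take the 6% row and assume 80% linkage among the 24 cases and 60% among the 4.8 extra cases. ART starts: 24 × 0.8 = 19.2 v 19.2 + 4.8 × 0.6 = 22.1. Linkage among the diagnosed falls from 80.0% to 22.08/28.8 = 76.7%, while ART starts per enrolled adult rise from 0.48% to 0.55%. In the 12%-base table the linkage comparison rests on about 24 to 34 people per arm.

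**Power on the all-enrolled outcome.** For 0.60% v 0.84% with 4,000 per arm, the same formula gives (0.1518 − 0.2344)/0.1196 = −0.69, so power is about 24%.

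**The case against.** The reach is limited. Section 2.6 determines the primary outcome and testing uptake for every enrolled adult, and these two answer the main objective on demand for testing. A reader might infer that randomisation fails for the trial as a whole. It does not: only two secondary comparisons are affected. This stands.

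Section 2.10 states no hypothesis for positivity or linkage, and multiplying uptake by positivity recovers cases per enrolled adult. This is fair, but section 2.10 still compares these outcomes between arms, and a reader should not have to rebuild the relevant quantity.

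A reader might say that section 2.6 flatly contradicts section 1.5. The Protocol never defines *yield*, and the word can mean positives per test. The firmer ground is the section 1.5 aim on finding newly diagnosed people, together with the yield of people starting ART, which linkage among the diagnosed does not clearly match.

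A reader might also infer that the positivity outcome counts people who already knew they were positive. Section 2.6 omits the word *new* there, but nothing in the Protocol shows that such people are tested or counted. This is a gap in wording and no more.

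Finally, a change of sign is possible but not certain, because it depends on an assumed positivity among extra testers. In the 5% row neither measure would separate the arms: 24/200 v 28/280 gives z = 0.70 (p about 0.49), and 24/4,000 v 28/4,000 gives z = 0.56 (p about 0.58). The gain from the change is a comparison that answers the question, not a powerful test.

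**Conclusion.** The point holds for two of the three secondary outcomes and should be fixed. The denominators are set in the Protocol itself, beside an outcome for which all enrolled adults are explicitly kept, so this is not a detail left open for a later analysis plan. The conditional comparisons are not randomised, and no defined outcome measures diagnoses or ART starts per adult enrolled.

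On the 12% base, conditional positivity falls while case finding rises for any positivity among extra testers above 0% and below 12%. At 12% it stays level while cases rise by 40%. These sizes rest on every presenter testing, on 12% positivity under standard of care, and on the intervention only adding testers; the direction depends on the risk of those added. The documents do not support saying that a reversal will occur, or that the primary result is at risk.

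**What to change.** In sections 2.6 and 2.10:

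- Define HIV-positive diagnosis (new diagnosis where prior status is recorded) and ART start after a positive test as yes/no outcomes for every enrolled adult, meaning everyone followed for the primary outcome. Count non-attenders as no.
- Use these as the between-arm comparisons and report them as estimates with confidence intervals.
- Keep positivity among the tested and linkage among the diagnosed as descriptive measures, labelled as non-randomised. They still answer a fair care-cascade question.
- Align the terms in the Summary and section 1.5 with these definitions.

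The cost is mainly wording and a small change of analysis. Envelopes distributed are already counted by study group (section 2.8), and test result and ART start date are already collected from consenting attenders (section 2.5). There are two drawbacks. Event proportions are below 1% in the 5% v 7% illustration, so intervals will be wide and power low. Separating new from known positives needs prior HIV status to be recorded at the practice. The visible text does not confirm this: the list of questions in section 2.5 is not exhaustive and the appendix forms are not shown. If prior status is not recorded, the screening log would need an added item, or the outcome should be named as any HIV-positive test.

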**Approach:** A randomized controlled trial to rapidly test two different low-cost demand creation interventions among adults residing in the catchment areas of GPCC programme clinics. For one group of participants, free HIV testing will be bundled with other health services that might be desired. Participants will receive a brochure that advertises the opportunity to receive free blood pressure testing and rapid glucose testing along with free HIV testing. This approach seeks to address stigma associated with HIV testing while also offering other health services that people value. For a second group of participants, the value of HIV testing will be emphasized using a 100 Rand voucher (US\$ 7) that can be redeemed for free services. This approach highlights the monetary value of the free services and seeks to leverage an endowment effect and loss aversion. A third group of participants will receive the standard of care promotion materials for HIV testing. The primary outcome will be presentation at the GP practice. Secondary outcomes will include HIV testing uptake, yield of new HIV-positive diagnoses, and yield of PLHIV who initiate ART. The study will be conducted at approximately five YCN GP practices in the Johannesburg Health District. We will seek to enrol 12, 000 adults in the vicinity of the GP practices who are willing to engage with a YCN field worker and willing to accept an envelope that contains one of the three HIV testing promotion strategies. The study duration will be approximately 10 months.

**Significance:** The standard marketing material (YCN brochure) and the YCN social media campaign have had limited success in increasing demand for HIV services offered by GP practices. There is a growing body of evidence from behavioural science showing that individuals' decision-making can be affected by the way in which information is presented and services are offered. We seek to test low-cost, easy-to-implement, demand creation strategies that can be implemented by the GPCC to increase demand for HIV services at GP practices.

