### **1.1 The HIV Care continuum in South Africa: where are the gaps?**

South Africa has built the world's largest HIV treatment program since starting to provide antiretrovirals in 2004. In 2020, there were an estimated 7.6 million people living with HIV (PLHIV) and 5.2 million (70%) were receiving antiretroviral therapy (ART) (1). Yet South Africa, like many countries, did not manage to reach the 90-90-90 targets by 2020 and is unlikely to reach the 95-95-95 targets by 2030 without further progress in expanding the utilization of HIV services. According to UNAIDS, 92% of PLHIV South Africans knew their status in 2020 but of those only 70% initiated treatment and of those 64% were virally suppressed (1). The General Practitioner Care Cell (GPCC) is an innovative, public-private partnership that seeks to increase coverage of ART among PLHIV by leveraging the resources in the private healthcare sector to reach uninsured individuals who are not accessing care.

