### **2.3 Study design and intervention**

We will conduct a randomized control trial to determine the effectiveness of the new demand creation materials in reaching new individuals for HIV testing and linkage to care at GP practices. Individuals will be randomized to one of the study arms and will each receive an envelope containing the relevant demand creation material for their arm. The YCN field workers will use the recruitment script (Appendix 4) to inform individuals about HIV testing services at the GP practice and distribute the envelopes in the community. The name of the GP and contact number of the GP practice will be stamped on each brochure. The three study groups will include:

**Study Group 1:** A brochure promoting a free healthy lifestyle screen which includes HIV testing. This brochure will offer individuals options for a healthy lifestyle screen (weight, height, blood pressure, rapid glucose and HIV test). This brochure will be in addition to the standard of care demand creation material.

**Study Group 2:** A patient voucher for HTS (and ART): A voucher redeemable for free services valued at ZAR100 (USD 7) for HTS and approximately ZAR5,048 (USD 337) for ART (based on eligibility). The voucher will emphasize the value of the services offered. This brochure will be in addition to the standard of care demand creation material.

**Study Group 3:** Your Care Network (YCN) brochure advertising free HTS and free ART (for those who test positive) and the name and telephone contact number of the GP practice. This approach also includes existing social media platforms.

The healthy lifestyle and the patient voucher brochures will be co-designed with the study team and key stakeholders. The study demand creation material will be prototyped as part of the existing routine GPCC programme. Revisions to the brochures will be made prior to study implementation. The brochures will be submitted to ethics for approval prior to study implementation.

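### The ART secondary outcome is given three different populations, so the plan does not settle whether previously diagnosed, untreated people who start ART count.

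*Protocol*

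**What the plan says.** The Study Summary (Approach) and section 1.5 list three secondary outcomes in the same words: "Secondary outcomes will include HIV testing uptake, yield of new HIV-positive diagnoses, and yield of PLHIV who initiate ART". Here the word new qualifies the diagnoses. The ART item covers people living with HIV, with no limit by date of diagnosis, and it is called a yield.

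Section 2.6, which defines the outcomes, moves that word. Positivity is now taken among everyone tested, with no mention of new diagnoses. The ART item becomes "Linkage to care among newly diagnosed individuals. We will assess whether participants who tested HIV-positive initiate ART at the GP practices". The first of these two sentences is limited to new diagnoses. The second, which states what will be measured, has no condition of new diagnosis. The data-handling text in section 3.7 likewise ties the linkage check to a positive test.

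Of the secondary outcomes in section 2.6, only testing uptake is expressly defined over all enrolled adults. Section 2.10 then compares the secondary outcomes of each intervention arm with standard of care by logistic regression.

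**The concern.** The three wordings give different answers for a person who already knows they have HIV, is not on ART, receives an envelope and starts ART at the practice. Such people are not excluded by section 2.2, and section 2.3 shows that the materials advertise ART as well as testing. The documents do not say how they are handled.

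The denominator is unsettled too. A yield is naturally read over everyone given an envelope, which keeps the randomised comparison. Linkage among those diagnosed or testing positive is a proportion within a group that exists only because people chose to attend and test, and the materials are meant to change that choice. A difference between arms in that proportion can reflect who came as much as what the material did.

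Events will be few, so the choice of definition could change the reported ART result, and the present text leaves that choice open until the data are seen.

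**Working it through.** **The plan's own figure.** No sample-size figure is stated for the ART outcome. The one calculation, in section 2.7, is for presentation at the practice. For 5% versus 7%, two-sided alpha 0.05 and 2,400 per arm, power is 83.1% (80% needs 2,213 per arm), so the stated power above 80% reproduces. It does not depend on this point.

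**The wordings side by side,** for someone who starts ART at the practice:

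| Person | Summary and 1.5 (people with HIV who start ART) | 2.6, first sentence (newly diagnosed) | 2.6, second sentence (tested positive) |
|---|---|---|---|
| Newly diagnosed at the practice | counts | counts | counts |
| Previously diagnosed, untreated, retests positive there | counts | does not count | counts |
| Previously diagnosed, untreated, not retested there | counts | does not count | does not count |

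Under the third wording, a person already on ART who retests positive also enters the denominator, although there is no new start to record.

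**Size of the affected group, national figures.** Section 1.1 states that "92% of PLHIV South Africans knew their status in 2020 but of those only 70% initiated treatment".

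- Undiagnosed: 1 − 0.92 = 0.08 of people with HIV.
- Diagnosed but untreated, taking 70% as a share of those diagnosed: 0.92 × 0.30 = 0.276.
- Diagnosed but untreated, taking 70% as a share of all people with HIV: 0.92 − 0.70 = 0.22. The same section also gives 5.2 of 7.6 million on ART, which is 68.4%; then 0.92 − 0.684 = 0.236, inside this range.
- Ratio to the undiagnosed: 0.22/0.08 = 2.75 to 0.276/0.08 = 3.45.
- Share of all untreated people with HIV: 0.22/0.30 = 73% to 0.276/0.356 = 78%.

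**Illustration per arm of 4,000.** Assumptions: 5% presentation under standard of care and 7% in an intervention arm (section 2.7), 12% HIV prevalence (Table 1), national shares holding among presenters, and every untreated presenter starting ART. The last makes these upper limits, given the others.

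| | Standard of care | Intervention arm |
|---|---|---|
| Presenters | 4,000 × 0.05 = 200 | 4,000 × 0.07 = 280 |
| With HIV | 200 × 0.12 = 24 | 280 × 0.12 = 33.6 |
| Newly diagnosed only | 24 × 0.08 = 1.9 | 33.6 × 0.08 = 2.7 |
| Diagnosed, untreated | 24 × (0.22 to 0.276) = 5.3 to 6.6 | 33.6 × (0.22 to 0.276) = 7.4 to 9.3 |
| All untreated | 7.2 to 8.5 | 10.1 to 12.0 |

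The tested-positive wording gives 1.9 + r × (5.3 to 6.6) under standard of care, where r is the share of diagnosed, untreated attenders who retest. The documents do not give r. At r = 0 this equals the newly diagnosed count; at r = 1 it equals the count for all untreated people.

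**Precision under the widest definition.** With 8.5 versus 12.0 starts, z is about (12.0 − 8.5)/√(12.0 + 8.5) = 3.5/4.53 = 0.77, or roughly 12% power.

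**The case against.** The strongest reply is that the Summary and section 1.5 are shorthand for a cascade of testing, diagnosis and treatment, which section 2.6 then spells out. The objective is demand for HIV testing, so linkage after a positive test fits it, and ART coverage is the programme's goal rather than the trial's estimand. This is a fair reading, but it does not settle which population applies, because the two sentences in section 2.6 disagree with each other.

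A reader might go further and infer that previously diagnosed people count in no ART outcome. The documents do not support that. The second sentence of section 2.6 counts anyone who retests positive, and sections 2.5 and 2.9 route attenders through consent for HIV testing. No route to ART without a test is described, so the group outside both sentences may be small.

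A reader might also infer that section 2.6 hides most of the ART benefit, or hides an advantage of the voucher arm, which prints a value for ART. That is not shown either. The shares are national and the mix among attenders is unknown. By section 2.3, both intervention arms also receive the standard material, which advertises free ART, so every arm is offered it.

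Finally, low power makes any definition close to descriptive. That is correct. It limits what the comparison can show, but it does not excuse leaving the count undefined.

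**Conclusion.** The inconsistency stands: one secondary outcome has three populations, with a shift from a yield to a proportion within a post-randomisation subset. What is undefined is whether previously diagnosed, untreated people count. Nationally they outnumber the undiagnosed by about 2.75 to 3.45 to 1, so the count could differ materially between definitions. How far it differs in this trial depends on two quantities the documents do not give: the mix of people who attend, and the share of those already diagnosed who retest. The illustrated range of about 2 to 8.5 starts under standard of care rests on the assumptions listed and is not a forecast. No bias towards or against any arm is established.

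The point should be corrected, but it is confined to a secondary outcome. The primary outcome and the sample size are untouched.

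**What to change.** In section 2.6, define the ART outcome as ART started at a GP practice during the study, taken from the ART start date in the Intelligent Care System, by a person not already on ART, whatever the date of diagnosis. Use all adults given a study envelope in that arm as the denominator; section 2.8 already counts envelopes by study group. Align the Study Summary and section 1.5 with this wording.

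Report the starts split into newly and previously diagnosed. Keep linkage among those newly diagnosed or testing positive as a descriptive outcome, with its denominator stated.

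The cost is a wording change plus two items at the GP visit: prior diagnosis and prior ART. Section 2.5 names neither, but its list is open and the enrolment log is not shown, so they may already be collected. Section 2.9 places entry in the enrolment log and the care system after both the study and testing consents are signed, so data capture must also cover consenting attenders who start ART without a retest. The comparison between arms will remain imprecise and should be presented as such.

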**Exclusion criteria:**

- Individuals who refuse to engage with an YCN field worker

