## **2.5 Recruitment procedures**

Each YCN field worker will use a recruitment script (Appendix 4) to engage with potentially eligible individuals and will then hand them a marked envelope. Individuals will be recruited individually or in groups. The handing out of brochures is a standard demand creation strategy and no informed consent will be obtained from individuals during this interaction. The field worker will only record basic demographics (age group, gender) on individuals who receive the study envelopes on the REDCap system. This will be completely anonymised and not linked to any personal identifying information and only used to determine aggregate statistics. YCN field workers will target areas in the GP's catchment area (or within a local taxi ride) specifically targeting high volume and high transit settings. Some recruitment sites will include the industrial zone/formal workspaces, informal workspaces (trading stalls, spaza's, salons, veggie stalls etc), retail/shopping zones, establishments that sell food, educational settings (TVET, university, trade schools, etc), commuter stops and other community settings (indoor and outdoor venues). We will be able to record which envelopes are distributed at the different recruitment sites on REDCap using the data fields on the distribution log (Appendix 5).

Individuals who are interested in the services provided by the GP and attend the GP practice will be asked about how they heard about the practice and requested to hand-in the brochure that they received. The individual will then be requested to sign a study consent form (Appendix 8 and

9) before any data is collected and sign an HTS consent form (Appendix 7) before any medical procedures. As part of the research study and routine procedures at the GP practice, we will ask participants some questions. Questions will include but are not limited to demographic information (age, gender, telephone number and primary home address) and HTS outcomes (Date of HIV test, HIV test result and ART start date).

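### The diagnosis outcome in section 2.6 counts every positive test although the objectives name new diagnoses, and the linkage outcome is worded in three incompatible ways

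*Protocol*

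**What the plan says.** Section 1.5 of the protocol (and the Approach paragraph of the Study Summary) gives the secondary outcomes as: "Secondary outcomes will include HIV testing uptake, yield of new HIV-positive diagnoses, and yield of PLHIV who initiate ART". Section 1.5 adds: "We will also examine the effect of the interventions on identification of newly diagnosed PLHIV".

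Section 2.6, which defines the outcomes, drops the word new from the diagnosis outcome: "HIV-positivity among participants who get tested for HIV". Its linkage bullet is labelled "Linkage to care among newly diagnosed individuals", but the sentence that says what will be measured is "We will assess whether participants who tested HIV-positive initiate ART at the GP practices".

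The only exclusion criterion in section 2.2 is "Individuals who refuse to engage with an YCN field worker". Adults who know they are HIV-positive, including those already on ART, are therefore eligible.

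The HIV items that section 2.5 names for collection at the practice are "HTS outcomes (Date of HIV test, HIV test result and ART start date". Section 3.7 names the same three. Neither names a previous positive result or previous ART. Section 2.5 does say that its list of questions is not exhaustive.

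**The concern.** Followed as written, the diagnosis bullet in 2.6 treats a re-test by a known-positive person as equal to the discovery of an undiagnosed one. That is a stated rule that does not measure the stated outcome, rather than a detail left for later.

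The linkage bullet allows two denominators, and section 1.5 supplies a third description that is not limited to new diagnoses. If the measuring sentence governs, people already on ART enter the denominator but cannot newly start, which pulls the proportion down for reasons unrelated to linkage. Two analysts could both comply and report different results.

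The denominator of positivity is people who choose to test, so randomisation does not balance the mix of known and undiagnosed people within it. The voucher displays the value of ART and the lifestyle brochure offers other screening (section 2.3). Either could draw known-positive people at a different rate from the standard brochure. Whether it would is not known. If it did, a difference in positivity between arms could not be read as a difference in finding undiagnosed people.

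**Working it through.** **The plan's own figure.** The protocol states power only for presentation: more than 80% with 2,400 per arm for a 2-point difference from 5%. For 5% against 7%, two-sided alpha 0.05, the normal approximation gives z = (0.02 × √2400 − 1.96 × √(2 × 0.06 × 0.94)) / √(0.05 × 0.95 + 0.07 × 0.93) = 0.958, so power is 83.1%. The figure reproduces. The present point does not rest on it, and no figure is given for the diagnosis or linkage outcomes.

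**Inputs from the protocol.** 4,000 per arm and 5% presenting under standard of care (2.7); 12% HIV prevalence (Table 1); "92% of PLHIV South Africans knew their status in 2020" (1.1); 70% of those aware having started treatment (1.1).

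**Assumptions.** All presenters are tested. Let r be the rate at which known-positive people present and test, relative to everyone else. The documents do not give r, so a range is shown.

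**Expected counts at r = 1.** Presenters: 4,000 × 0.05 = 200. PLHIV: 200 × 0.12 = 24. Aware: 24 × 0.92 = 22.1. Unaware: 24 × 0.08 = 1.9.

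**Break-even.** Known positives outnumber new diagnoses when 0.92r > 0.08, that is r > 0.08/0.92 = 0.087.

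**Share and positivity.** New share of positives = 0.08/(0.08 + 0.92r). Positivity among those tested = 0.12(0.08 + 0.92r) / [0.88 + 0.12(0.08 + 0.92r)]. New diagnoses per 200 presenters = 200 × 0.0096 / [0.88 + 0.12(0.08 + 0.92r)].

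| r (assumed) | Positivity | New share of positives | New diagnoses per arm |
|---|---|---|---|
| 0 | 1.1% | 100% | 2.2 |
| 0.10 | 2.3% | 46% | 2.1 |
| 0.25 | 4.1% | 26% | 2.1 |
| 0.50 | 6.9% | 15% | 2.0 |
| 1.00 | 12.0% | 8% | 1.9 |

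Positivity moves from 1.1% to 12.0% while new diagnoses stay at about 2 per arm. At 7% presentation (280 presenters) the count is about 3. As an illustration, an arm with r = 0.25 beside an arm with r = 0.10 would show 4.1% against 2.3% positivity with practically the same number of new diagnoses.

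**Linkage, if all positives form the denominator.** Assume that treated people re-test as often as aware but untreated people, and that every untreated person starts ART. The highest attainable proportion is 1 − 0.70 × (1 − new share): 63%, 48%, 40% and 36% at r = 0.10, 0.25, 0.50 and 1.00. Section 1.1 also gives 70% as the share of all PLHIV on ART; on that reading the ceiling at r = 1 is 1 − 0.70 = 30%.

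**The case against.** Several points on the other side stand.

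- A reader might infer that both outcomes count anyone who tests positive. The documents do not support that for linkage. Its label limits it to the newly diagnosed, and the next sentence can be read as referring back to them. The defect there is inconsistent wording, not an unqualified count.
- A reader might infer that new and known positives cannot be told apart. That is not established. The question list is open, and the screening log and HTS consent form (Appendices 6 and 7) are not shown. ICS holds longitudinal records of identified GPCC patients (3.7). An ART start date before the test date, if captured, would reveal some people already treated. None of these is stated to identify a diagnosis made outside the programme in someone not on ART.
- Section 1.5 states the objective as demand for testing; new diagnoses are a secondary outcome. Its ART outcome covers all PLHIV who start, so restricting linkage to new diagnoses alone would discard ART starts among known but untreated people.
- The re-test rate is assumed. Below 8.7% known positives are a minority, and at 10% the split is close to even.

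It can also be said that the rule for calling a diagnosis new belongs in an SAP or operating procedure. That answers a missing detail, but section 2.6 does state a definition, and it differs from the outcome named in 1.5. Nor can a later analysis recover prior status if the visit did not record it.

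**Conclusion.** The point holds in a limited form. The diagnosis outcome as defined in 2.6 does not measure the new diagnoses named in the Study Summary and section 1.5, and the three wordings of the ART outcome need to be reconciled. On the listed items alone prior status is not recorded, but the unseen forms may already ask for it.

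It would go too far to say that known positives will dominate the results. They would be the majority of positives only if they test at more than about 8.7% of the rate of undiagnosed people. Over an assumed 10% to 100%, new diagnoses would be 46% to 8% of positives. These figures rest on 12% prevalence, 92% awareness, 5% presentation and all presenters being tested.

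Both outcomes are secondary. Presentation, its power and testing uptake are unaffected. With about 2 new diagnoses expected per arm, no definition will support a firm comparison between arms. What the correction protects is the meaning of the reported count.

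**What to change.** 1. In section 2.6, define the diagnosis outcome as a positive test in a person with no previous positive result and no previous ART.
2. Unless the forms already ask, add two yes/no items to the screening and enrolment log: previous HIV-positive result, and previous or current ART. Ask them at the practice after consent and check the answers against ICS.
3. Reconcile the linkage wordings. Report ART start among the newly diagnosed and, separately, among previously diagnosed people not on ART, so that the outcome in section 1.5 is kept. Leave people already on ART out of both denominators.
4. Report new and known positives separately by arm, and describe the comparison of new diagnoses between arms as descriptive.

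The cost is at most two questions on an existing REDCap form and some rewording; if the forms already hold the items, it is rewording only. The drawbacks are that prior status is partly self-reported and that the event counts become very small.
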